### **Follow up procedures**

After initially recording an AE or recording and reporting an SAE, the local PI will follow each participant's medical progress. Follow up information on an SAE should be reported to the TOPSY Study Glasgow Office when received.

AEs still present in participants at the last study appointment should be monitored until resolution of the event or until no longer medically indicated (as confirmed by the local PI).

## **11. END OF STUDY**

The end of study is defined as the receipt of the last participant's 18 month follow up data. The end of the study will be reported to the REC, and R&D Offices and the sponsor within 90 days, or 15 days if the study is terminated prematurely. The investigators will inform participants of the premature study closure and ensure that the appropriate follow-up is arranged for all participants involved.

A summary report of the study will be provided to the REC within one year of the end of the study.

## **12. CONTINUATION OF INTERVENTION FOLLOWING THE END OF STUDY**

When participants attend their appointment at 18 months, they will have a discussion with their healthcare professional about future care, including discussion about pessary self-management if this is desired and is an option locally. If a woman does not attend the 18-month appointment, the local recruitment officer will contact her to arrange a further appointment to ensure follow-up care is in place.

## **13. INDEMNITY**

The Participant Information Leaflet provides a statement regarding indemnity for negligent and non-negligent harm.

Pessaries have been used in the NHS for many years and are a relatively safe intervention. Self-management is a system used widely in health care and no serious ethical issues are foreseen. Potential risks relate to possible serious pessary complications, specifically: fistula, incarceration of pessary, occurrence of vaginal cancer. Incarceration of pessary, fistulae and rare reported cases of cancer are associated with the pessary not being removed and replaced for a prolonged period of time. As participants (self-management group and standard care group) are asked back to clinic at 18 months this is the longest that a participant should have a pessary in situ and very long periods without care are avoided.

Participation in the study will help evaluate the training and teaching procedures and effectiveness of self-management. Taking part in this study does not affect normal legal rights. Whether or not women take part, the same legal rights apply as any other patient in the NHS (which includes professional indemnity insurance for negligence). If a participant wishes to complain about their health care or any aspects of this study, the normal NHS mechanisms will be available.

In addition, the universities involved with the trial hold and maintain a 'no fault' insurance policy. This policy covers all employees of the universities and those working under their direction.

## **14. PUBLICATION AND DISSEMINATION**

The success of the trial depends entirely on the collaboration of a large number of women having pessary treatment for prolapse, as well as their healthcare team. For this reason, chief credit for the trial will be given, not to the committees or central organisers, but to all those who have collaborated in the trial. A trial publication policy will be developed. The results of the trial will be reported first to study collaborators.

The main funders report will be drafted by the Project Management Group and circulated to all collaborators for comment. The final version will be agreed by the Trial Steering Committee before submission for publication, on behalf of all the TOPSY collaborators. To safeguard the integrity of the main trial, reports of any explanatory or satellite studies will not be submitted for publication without prior agreement from the Project Management Group. Interest will be maintained in the trial by publication of newsletters at intervals for participants, staff and collaborators. Once the main report has been published, a lay summary of the findings will be sent to all involved in the trial.

To maximise the impact of the research, findings will be published in both practice based and high quality academic journals (such as The Lancet). Social media will be used to enable rapid dissemination of research results. The training manuals and any other training materials will be made freely available online and training days will be arranged. Where possible the PPI representatives will be involved in dissemination activities (training days, conference presentations).

## **APPENDIX B: The TOPSY study consent pathways.**

The following five flow charts diagrammatically outlines the individual recruitment and consent pathways. The pathways are arranged chronologically. The Participant Information Leaflets (PILs) and consent forms used are summarised below and are referenced in the relevant flow chart.

1. **PIL and Consent 01:** for the process evaluation, audio-recording of recruitment session between potential trial participants and the local recruiter (n=12-18 women in pilot study only)
2. **PIL and Consent 02:** for the main TOPSY trial (n=330 women), including an individual item on the consent form that asks for consent relating to the process evaluation for audio-recording of self-management teaching sessions (n=30 women) and follow up phone calls (n=30 women) and willingness to be approached for an interview study.
3. **PIL and Consent 03:** for the process evaluation, interviewing women who are randomised and have initialled the statement on the main trial consent form indicating that they are willing to be approached for interview study (n=36 women; 2 interviews each): self-management group (n=18 women) and standard pessary care group (n=18 women).
4. **PIL and Consent 04:** for the process evaluation, interviewing women who are potential participants but who decide not to take part in the main TOPSY trial (n=20 women)
5. **PIL and Consent 05:** for the process evaluation, interviewing health care professionals from TOPSY centres (aiming for a minimum n= 2 staff per centre, one staff member involved in recruiting women and one staff member who delivers the standard care and/or self-management intervention).

## Appendix B, Section 1:

### TOPSY CONSENT pathway 1: Audio-recording of recruitment discussion n=12-18 Audio-recordings

Part of the process evaluation in the pilot study only (2-3 per centre).

[figure not shown]

## Appendix B, Section 2

### TOPSY CONSENT pathway 2: Consent to the main study (n=330 women)

Note: Recruitment packs consists of; Main Trial PIL 02, invitation letter, expression of interest form 02 and reply-paid envelope.

[figure not shown]

### Appendix B, section 3:

#### TOPSY CONSENT pathway 3: Consent for woman to interview

(n=36 women): self-management group (n=18 women) and usual pessary care group (n=18 women)

[figure not shown]

**Note:** Prior to 18 month interview participants will be contacted and consent to continue with 18-month interview will be checked verbally and a suitable time arranged to complete the second face-to-face interview.

#### Appendix B, section 4

#### TOPSY CONSENT pathway 4: Consent for interviewing non-randomised women (n=20)

[figure not shown]

## Appendix B, section 5

### TOPSY CONSENT pathway 5: Consent for interviewing health care professionals from TOPSY centres

[figure not shown]

## **APPENDIX C- TOPSY COVID-19 Protocol Annex**

At the time of the COVID-19 Pandemic, recruitment to TOPSY is complete. This document describes any differences in the processes undertaken during this time to make sure that there are no safety concerns and that the data integrity remains as high as possible.

The original text from the applicable sections in the protocol are noted first and then any changes to the process documented in red immediately after.

### **Section 5.4 retention methods**

Active measures to minimise loss to follow-up of participants include:

- Recording at the outset women's email addresses and mobile phone numbers, their preferred method of contact (for follow up contact) and their preferred method of completion of questionnaires. Questionnaires can be completed online (via an email link) or in paper format and returned by post.
- Participants who do not return their questionnaires within three weeks will be sent up to three reminders using a variety of methods (post/email/ text message dependent on participants preferred method). The third reminder will be by telephone where the researchers will aim to gather the primary outcome data during the call.

Response rates to the self-reported questionnaires will be monitored to ensure they remain above 80%. If response rates are seen to drop, the team will discuss appropriate actions with the Project Management Group. Relevant action may include phone calls at different times of day or asking women to only complete the primary outcome measure.

### **Section 5.4 retention methods (during COVID-19)**

Questionnaires which were sent the week before "lockdown" will not have the first and 2nd reminders sent. Returned questionnaires are kept securely in the mail room at Glasgow Caledonian University and are delivered in batches to the data coordinator's house (these questionnaires do not contain patient identifiable information). For those who have not responded at the third reminder time-point, staff from the TOPSY office will call women to try and complete the questionnaires over the phone. For centres where letters of access are required for researchers to make these calls (very few), the centres will be asked to call the

women (if we know that resource is not an issue due to COVID-19) or the qualitative researcher (who has the relevant letters of access for each centre) will call the women. During the call, women will be offered the options of completing the questionnaire over the phone or if they provide an email address a link can be sent to them to complete online.

From the 11th May 2020, a member of the TOPSY team will access the study office and post out batches of questionnaires on a 6 weekly basis. For all batches of questionnaires sent from this date, reminder 1 (sent 3 weeks after the initial questionnaire) **will not** occur. We will post out a reminder at 6 weeks (previously the 2nd reminder) and then the 3rd reminder will be undertaken by phone as described previously.

A letter is being sent to all TOPSY participants with a COVID-19 update. In this letter it is stated that if a woman wants to complete her questionnaires online, rather than in paper format, she can email the TOPSY office with her email address.

If access to the TOPSY study office is stopped due to the continuing pandemic and we are unable to post out any further follow up questionnaires we will then explore the option of emailing links to all women we have email addresses for and calling those women we do not have email addresses for if they are due a follow up.

## **6.2 Standard pessary care**

Women will receive a clinic appointment for their pessary care according to the local management pathway. Content of appointments will follow local protocol which usually includes vaginal examination being performed to remove the pessary, inspection of the vaginal tissues and insertion of a new pessary. Data on frequency of appointments and of pessary changes at appointments will be recorded in the CRF. Healthcare professionals who deliver standard pessary care at each centre will be interviewed as part of the process evaluation allowing variation in standard pessary care to be described.

## **6.2 Standard pessary care (during COVID-19 update)**

All 21 centres have postponed pessary clinics for at least 3 months. All centres have let women know (either by letter or a phone call) what to do if they have any issues with their pessaries. Some centres are calling women when they would be due a follow up appointment to do a remote telephone follow up. If this happens, we are asking centres to complete the Telephone Support Log Form (CRF 07) which will capture the information that would be

collected if they attended clinic. If centres are not calling women as part of their standard care pathway we are not asking them to complete this CRF.

If women in the standard care arm call the centre and ask them to post a pessary out to them or to ask if they can attend their GP to get a pessary change, centres are asked to complete the Telephone Support Log Form (CRF 07) to capture this information. This information may be completed retrospectively.

### **7.1.3 Non-Validated secondary outcome measures**

#### **Uptake of telephone support related to pessary use**

Using a Telephone Support Log Form we will ask the intervention HCP who receives women's calls to record frequency and details of all calls received to the telephone support line. There will be a question in the pessary complication questionnaire that asks ALL women if they required telephone support as some women in the standard care group may also telephone for support from their local team. This will support understanding of adherence, effectiveness and level of support relating to the trial interventions.

#### **Uptake of telephone support related to pessary use (COVID-19)**

As detailed in 6.2 the Telephone Support Log Form (CRF 07) will also be used if centres call women to do telephone follow ups during COVID-19.

**Health of vaginal tissues:** At baseline and 18 months, women will have a vaginal examination undertaken at the clinic by a healthcare professional to assess the health of the vaginal tissues and identify problems associated with pessary use, for example, tissue granulation or ulceration.

#### **Health of vaginal tissues (COVID-19)**

As all pessary clinics are postponed women can't attend their end of study (18 month) clinic visit to get their health of vaginal tissues checked. The following was proposed for all 18

month TOPSY end of study visits and has been approved by the sponsor and was rolled out to all centres on the 21st April 2020.

Since all centres have postponed pessary management clinics the TOPSY 18 month appointments will now be split into 2 parts;

1. Part 1- a telephone call where all end of study questions on the clinic visit from will be completed over the phone.
2. Part 2 – a clinic visit (when clinics are back up and running post COVID-19) where the vaginal examination will take place.

Centres who are due 18 month appointments in the next few months have all verbally agreed that they have the resource to call all women at 18 months. If during the pandemic resource at centres is affected and they are unable to call these women there are 2 options;

- a) The lead urogynaecologist specialist nurse and co-applicant in Manchester could make the calls to these women to complete the 18 month visit over the phone. The nurse specialist would assess any safety concerns, report these to the relevant centre and thereby reduce any risks to participants of the centres not being able to contact these women.
- b) If the lead urogynaecologist specialist nurse is unavailable or the centre would prefer, the process evaluation researcher (University of Stirling) has all the necessary letters of access in place for all centres. She could make the calls and report the clinical questions back to one of the clinical members of the research team at Manchester (most likely a clinical research fellow working with one of the Chief Investigators ([name])).

## **APPENDIX D - TOPSY 4 year follow up Protocol Annex**

This annex describes the process of an additional 4-year follow up for TOPSY participants. This is an additional follow up time-point beyond the original funded 18 month end point.

### **Background and rationale for longer term follow up**

All original objectives set out in the main protocol (Version 7, dated 23rd November 2020) for the 18 month TOPSY study will be met. This includes data on the effectiveness and cost-effectiveness of self-management when compared to standard care on the quality of life for women with pelvic organ prolapse (hereafter prolapse) at 18 months. However, following the current cohort of women in the TOPSY study for up to 4 years would provide evidence addressing four of the top 10 James Lind Alliance (JLA) uncertainties for pessary care (Lough et al, 2018) specifically:

- Priority number 1. How might a pessary affect sexual activity?
- Priority number 2. Do pessaries have an effect on the psychological well-being of women?
- Priority number 4. What are the risks and complications of pessary use for prolapse?
- Priority number 5. Are pessaries effective as a long-term treatment for prolapse?

The top 10 JLA priorities have been identified since TOPSY was commissioned. It is clear from those priorities that women, health care professionals and other relevant stakeholders have long-term follow up as a core issue for future pessary management.

### **Research question (RQ)**

This RQ is supportive of, and additional to, the original TOPSY trial. The long term follow up research question is:

- What is the longer term (4 years) clinical-effectiveness and cost-effectiveness of self-management of vaginal pessaries to treat pelvic organ prolapse, compared to standard pessary care on condition specific quality of life?

All women in TOPSY completed a series of outcome measures combined into one questionnaire at baseline, 6, 12 and 18 months. The questionnaire booklet for the 4-year follow up will contain the same series of outcome measures as the 18 months booklet with the addition of some questions about pessary use between 18 months and 4 years and the IPAQ-E questionnaire as a measure of physical activity.

The sections below are extracts from the main protocol and outline the updated sections within that original protocol (version 7, 23rd November 2020). These changes will apply to the 4-year follow up. They are documented here for clear identification of the additions.

## **4. STUDY POPULATION**

### **4.1 Sample Size Calculation**

As the primary outcome measure (PFIQ-7) remains unchanged then the sample size calculation for the original trial still applies to the long term follow up. We will conduct an intention to treat analysis including all 340 randomised participants, with imputed values for non-respondents, which will provide more than 90% power based on our original assumptions regardless of response rate at 4 years. If 264 women respond out of the 292 women who have consented to be approached at 4 years (90% response rate), then an observed cases analysis will also have 90% power (with two-sided alpha of 5%) to detect a difference in means of 20 points on the PFIQ-7 between the standard care and self-management groups, assuming a standard deviation for PFIQ-7 at 4 years of 50. We anticipate a high response rate given the current levels of retention, however a response rate of at least 65% would still provide more than 80% power in an observed cases analysis.

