## **4. STUDY POPULATION**

### **4.1 Sample Size Calculation**

A sample size of 330 women (165 per group) is required to provide 90% power to detect a difference of 20 points in the PFIQ-7 score at 18 months, assuming a standard deviation of 50, two-sided alpha of 0.05, and 20% loss to follow-up. In order to detect this standardised effect size of 0.4 SDs (20/50 points), 132 women will need to be recruited per group, or 165 per group to allow for dropout. Since the identified centres each see approximately 35 women a month for pessary care, we aim to recruit two to three women per month per centre.

The aim is to recruit a sample size sufficient to detect a 20-point difference in the PFIQ-7 score (the potential range of the PFIQ-7 is 0 to 300), although we acknowledge that an appropriate minimum clinically important difference for PFIQ-7 has not been formally determined. Barber et al. (2005) suggested a minimum clinically important difference (MCID) of 36 points, but it was emphasised that this was based on a small sample and applies only to within-group rather than between-group differences. Therefore, as part of the internal pilot, we will canvass PPI, investigators, and other participating clinicians to gauge the perceived importance of a 20-point difference.

Two recent trials which have used PFIQ-7 in populations of women using pessaries have reported SDs at 12 months and 24 months between 25 and 40 (Weigersma et al., 2014; Panman et al., 2016). These studies however were relatively small, conducted in only a few centres, and neither measured PFIQ-7 at 18 months. Given this uncertainty, a conservative assumption that the SD may be as high as 50 has been made. This will be monitored by examining the variability in the PFIQ-7 score for those women recruited in the internal pilot and we will continue to monitor the aggregated (blinded) SD regularly (every 40 cases using six-month outcome data; and as cases complete at 18 months), with a view to re-estimating the sample size at an appropriate point if required.

A sample size of 330 also provides power for the analysis of secondary outcomes, e.g. we will have more than 90% power (2-sided 5% level of significance) to detect a 20% difference in pessary use continuation rate (assuming at least 50% in the standard care group continue to use a pessary at 18 months).

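### The 4-year annex claims more than 90% power at any response rate because missing scores will be imputed; no valid imputation can deliver that

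*Protocol*

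**What the plan says.** Protocol Appendix D (the 4-year follow-up annex), section 4.1, carries the original sample size calculation over to 4 years and makes three power statements.

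- The full analysis counts everyone who was randomised, 340 women in total. Its power is described in these terms: "with imputed values for non-respondents, which will provide more than 90% power based on our original assumptions regardless of response rate at 4 years".
- For observed cases at the hoped-for response, 264 of the 292 who may be approached (90%), the annex claims "90% power (with two-sided alpha of 5%) to detect a difference in means of 20 points on the PFIQ-7". The SD is again taken as 50.
- For observed cases at lower response, it says that "a response rate of at least 65% would still provide more than 80% power in an observed cases analysis".

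The original assumptions it invokes are in section 4.1 of the main protocol. The target there is a 20-point difference in PFIQ-7, with the remaining inputs given as "assuming a standard deviation of 50, two-sided alpha of 0.05, and 20% loss to follow-up". The size that results is stated separately: "132 women will need to be recruited per group, or 165 per group to allow for dropout".

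**The concern.** The first statement counts all 340 women as carrying 4-year information once their values have been imputed. Imputation adds no information about a woman's 4-year score beyond what her earlier data already hold. If it is done properly, the standard error grows with the number missing, so power must depend on how many women respond and on how well earlier scores predict the later one. Power for 340 at any response could be reached only by analysing imputed values as though they had been observed, and then the standard error is too small.

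The statement also conflicts with the calculation it relies on. The original design inflates 132 per group to 165 for loss to follow-up, which treats a missing outcome as lost information. If imputation restored full power, no inflation would have been needed.

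Two things are at stake. A null 4-year result from a depleted sample could be read as conclusive because the protocol promised over 90% power. And if the analysis were carried out in the only way that matches the promise, the confidence interval would be too narrow and the type I error inflated. Some non-response is certain: 340 − 292 = 48 women (14%) cannot be approached at all.

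**Working it through.** **Inputs.** Difference 20, SD 50 and two-sided alpha 0.05 (main protocol section 4.1, repeated in Appendix D section 4.1). Randomised 340, taken as 170 per group; approachable 292; target respondents 264 (Appendix D section 4.1). The correlation ρ between the 4-year score and earlier PFIQ-7 scores is not given, so it is an assumption here, shown over a range.

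**1. Reproduce the protocol's figures (normal approximation).**

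- n per group = 2(1.960 + 1.282)² × 50² / 20² = 131.3, so 132. Dividing by 0.8 gives 165. Both match.
- 264 respondents: SE = 50√(2/132) = 6.155; power = Φ(20/6.155 − 1.960) = 90.1%. This matches (89.9% by t-test).
- 340 all observed: SE = 50√(2/170) = 5.423; power = Φ(20/5.423 − 1.960) = 95.8%. The full-analysis claim matches only this complete-data case.

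**2. Power when non-respondents are validly imputed.** Assume missing at random, earlier scores complete for all 340 (a generous assumption), and m respondents per group:

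Var(difference) = 2 × 50² × [(1 − ρ²)/m + ρ²/170]

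With ρ = 0 this reduces to the observed-cases variance. Worked example for 146 respondents (m = 73) and ρ = 0.6: 5000 × (0.64/73 + 0.36/170) = 54.42, so SE = 7.377 and power = Φ(20/7.377 − 1.960) = 77.4%.

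| Respondents | % of 292 | ρ = 0 (observed cases) | ρ = 0.5 | ρ = 0.6 | ρ = 0.7 |
|---|---|---|---|---|---|
| 264 | 90 | 90.1% | 91.7% | 92.3% | 93.1% |
| 236 | 81 | 86.7% | 89.2% | 90.3% | 91.5% |
| 200 | 68 | 80.7% | 84.8% | 86.5% | 88.6% |
| 190 | 65 | 78.7% | 83.2% | 85.2% | 87.6% |
| 146 | 50 | 67.6% | 74.2% | 77.4% | 81.3% |
| 117 | 40 | 58.1% | 65.8% | 69.7% | 74.7% |
| 68 | 23 | 37.8% | 45.4% | 49.8% | 56.2% |

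At ρ = 0.9, 146 respondents would give 90.9%, but 68 would still give only 79.4%. The response needed for 90% power, as a share of the 340, is about 77% at ρ = 0, 72% at 0.5, 64% at 0.7, 55% at 0.8 and 39% at 0.9. It never vanishes.

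**3. Check by simulation.** Multiple imputation was simulated with 20 imputations, variances combined by Rubin's rules and 1000 replicates (Monte Carlo error about 1.5 points). At 56% response of 340 (190 women), power was 77%, 81% and 85% for ρ = 0, 0.5 and 0.7. At 40% it was 59%, 69% and 76%; at 20%, 33%, 39% and 54%. The pattern agrees with the formula.

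**4. The 65% sentence.** The paragraph sets its response rate on 292, since 264/292 = 90.4%. On that base 0.65 × 292 = 189.8, so 190 women: SE = 50√(2/95) = 7.255 and power = Φ(20/7.255 − 1.960) = 78.7% (78.3% by t-test). Reaching 80% takes 2(1.960 + 0.842)² × 50²/20² = 98.1 per group, about 197 women. By t-test it takes 99.1 per group, about 199. That is 67% to 68% of 292. On a base of 340, 65% is 221 women and 84.5%, and the sentence would hold.

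**The case against.** The clause itself cannot be defended, but several points limit how much hangs on it.

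- **The type I harm is conditional.** Appendix D names no imputation method, and its section 8.1 puts the 4-year analysis under a pre-specified plan in line with the original trial. Main protocol section 8.1 uses a repeated measures mixed model under missing at random, with pattern-mixture and complete-case sensitivity analyses. Nothing says imputed values will be analysed as observed, and the method may properly sit in the SAP. This stands: inflation is a risk if the claim is followed, not a stated plan.
- **Response is not neglected.** The annex keeps the retention measures of section 5.4 and adds a randomised sub-study of pre-notification (Appendix E). This also stands, but it does not make the power figure right.
- **No design decision rests on it.** Recruitment is finished, the 18-month primary analysis is untouched, and at 264 respondents power is about 90% or better. True; the claim fails below the anticipated response, which is exactly the case its wording is meant to cover.
- **The shortfall may be smaller than shown.** Adjusting for baseline scores adds precision. With an assumed baseline correlation of 0.5, the residual SD is 50√0.75 = 43.3, and 190 respondents give about 89%. The protocol calls SD 50 conservative and cites 25 to 40; at SD 40, 190 observed cases give 93%. But the annex rests its claim on the original assumptions, and even at SD 40, 117 observed cases give 77% and 68 give 54%. Power still depends on response.
- **The 65% slip is small.** It is about 1.3 points and some seven women by the protocol's own approximation, and it disappears on a base of 340. This stands; it is a minor correction.

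**Conclusion.** The concern holds. The stated power for the 4-year intention-to-treat analysis is wrong as written: the figure is the complete-data power for 340 women (95.8%), and no valid imputation keeps it above 90% whatever the response. At 146 respondents it is about 68% with uninformative earlier scores and 74% to 81% for correlations of 0.5 to 0.7. These figures rest on SD 50, a 20-point difference, equal groups, data missing at random, and a correlation that the protocol does not give. The conclusion that power depends on response does not rest on any particular correlation.

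The 65% statement also misses its floor on the paragraph's own denominator (78.7%), but only narrowly. Imputation or a mixed model can recover part of the lost information, and at the target of 264 respondents the design has about the power claimed. The error is in presenting that power as guaranteed.

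**What to change.** In Appendix D, section 4.1:

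1. Delete the clause that makes power independent of the 4-year response.
2. Replace it with a short table of observed-cases power by number of respondents, for example 264 (90%), 236 (87%), 200 (81%), 190 (79%) and 146 (68%). If power with imputation is also shown, state the assumed correlation and give a range.
3. State that power rests on the women who respond, and that imputation or the mixed model recovers only part of what is lost.
4. Change the 65% to about 68% (some 200 of 292 women), or keep 65% and state about 78% to 79%, or say that the base is 340 if that was meant.
5. State that any imputation will be multiple with variances combined, or that the missing-at-random mixed model of main protocol section 8.1 will be used. The details can stay in the SAP.

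The cost is rewording one paragraph and accepting a less favourable power statement. No extra participants, data or follow-up are needed.
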